	**491.8 Other chronic bronchitis**	
	**496 Chronic airway obstruction, not elsewhere classified**	

ICD = International Classification of Diseases, with modifications approved by the World Health Organization

ICPC = International Classification of Primary Care (WONCA – World Organization of Family Doctors)

Additionally, a cohort will be selected in order to analyze the clinical and health-care variables. These patients must also meet the following additional inclusion criteria: 1) be able to perform spirometry; 2) meet spirometry criteria for a diagnosis of COPD: lung disease characterized by irreversible airflow limitation defined by a ratio of forced expiratory volume in 1 second [FEV_1_] to forced vital capacity ≤70% after a negative bronchodilator test, and in case of a positive postbronchodilator test (an increase in FEV_1 _of >12% and >200 mL after the use of 400 μg of salbutamol) not having a personal history of asthma, symptoms of atopy or a smoking habit of <40 pack-years. Additional exclusion criteria for this cohort were 1) a diagnosis of any terminal disease that indicates a survival prognosis <6 months, 4) advanced heart failure, 5) sequelae of pulmonary tuberculosis, and 6) lung cancer. All patients will have to give their written, informed consent to be enrolled.

Patients with other respiratory or nonrespiratory diseases can be included in the study provided they do not interfere with measurements. The testing of patients in a period of COPD exacerbation will generally be postponed until the disease has been stable for at least one month. Patients with exacerbated disease will not be excluded from the study, however; in case of continuously recurring exacerbations, the patient will be tested in that clinical state.

Calculation of the cohort size: For two-tailed comparisons, accepting an alpha risk of 0.05 and a beta risk of 0.2, to detect a statistically significant between-group CRQ score increment of 0.5 points (the minimum clinically significant difference) [38], and assuming a homogeneous standard deviation of 1.7 and a loss to follow-up of 10%, we have calculated that 220 patients will be required in each cohort. A simple random sampling procedure will be used to select the cohort patients.

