**Methods/Design:**

A quasi-experimental study of the effectiveness of a COPD management model called COPD PROCESS. The patients in the study cohorts will be residents of neighborhoods served by two referral hospitals in Barcelona, Spain. One area comprises the intervention group (n = 32,248 patients) and the other the control group (n = 32,114 patients). The study will include pre- and post-intervention assessment 18 months after the program goes into effect. Analyses will be on two datasets: clinical and administrative data available for all patients, and clinical assessment information for a cohort of 440 patients sampled randomly from the intervention and control areas. The main endpoints will be the hospitalization rates in the two health-care areas and quality-of-life measures in the two cohorts.

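### The stated sample-size inputs give about 203 patients per cohort, not the 220 said to be calculated from them; the discrepancy is conservative

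*Protocol article*

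**What the plan says.** The calculation is in the protocol article, Methods/Design, under Type of participant, in the paragraph on cohort size. The error rates are given as "For two-tailed comparisons, accepting an alpha risk of 0.05 and a beta risk of 0.2". The target is "to detect a statistically significant between-group CRQ score increment of 0.5 points (the minimum clinically significant difference"). The sentence then continues: "assuming a homogeneous standard deviation of 1.7 and a loss to follow-up of 10%, we have calculated that 220 patients will be required". The number is per cohort.

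The Abstract (Methods/Design) gives the total to match: "clinical assessment information for a cohort of 440 patients sampled randomly from the intervention and control areas". The Statistical analysis section plans to compare quality of life with the control group by a test of two independent means, which is the test that the usual formula assumes. Quality of life is named in the Background as one of the two principal endpoints.

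The article mentions no design effect, multiplicity correction, rounding-up rule or safety margin for this number.

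**The concern.** The article lists every quantity the calculation needs and presents 220 as its result, so it can be checked without outside figures. It does not check out: the same inputs give a number about 8% smaller. This is the only sample-size justification in the article, and it supports a principal endpoint. A reader who tries to reproduce it cannot tell whether the SD, the loss rate or the power is the real design assumption, or whether a margin was added. These possibilities differ in what they imply. If the stated inputs are right, the cohorts have some spare power. If a larger SD or a higher loss was expected, they may have none.

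**Working it through.** **Inputs** (all from the cohort-size paragraph): two-sided alpha 0.05, so z = 1.960; power 0.80, so z = 0.8416; difference 0.5; common SD 1.7; loss 10%; equal groups.

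**Step 1: evaluable patients per cohort.**
n = 2 × (1.960 + 0.8416)² × 1.7² / 0.5² = 2 × 7.849 × 11.56 = 181.5, so 182. The t-test version gives 182.4, so 183.

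**Step 2: allow for 10% loss.**
- Dividing by 0.9: 182 / 0.9 = 202.2, so 203. The t-test version is 183 / 0.9 = 203.3, so 204.
- Multiplying by 1.1 instead: 181.5 × 1.1 = 199.6, so 200; or 182 × 1.1 = 200.2, so 201.

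The result lies between 200 and 204 under any of these conventions. The stated 220 is not reproduced.

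**Step 3: size of the gap.**
220 − 203 = 17 per cohort, and 17 / 203 = 8.4%. In total, 440 against 2 × 203 = 406.

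**Step 4: what 220 delivers on the stated inputs.**
220 × 0.9 = 198 evaluable. The standard error of the difference is 1.7 × √(2/198) = 0.1709, and 0.5 / 0.1709 = 2.926. Power = Φ(2.926 − 1.960) = Φ(0.966) = 83.3%, or 83.1% by the t-test. The difference detectable with 80% power is 2.8016 × 0.1709 = 0.479. All of this treats patients as independent.

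**Step 5: could ordinary variants explain 220?** All use the stated 10% loss, by division, and round up.

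| Variant | Enrolled per cohort |
|---|---|
| One-sided alpha 0.05 | 159 |
| SD of 1.65 to 1.75 (the values that round to 1.7) | 190 to 215 |
| Rank test, efficiency 0.955 | 212 to 213 |
| Rank test, efficiency 0.864 | 234 to 235 |
| Power 0.85 | 232 |
| Power 0.90 | 270 |
| Alpha 0.025 | 245 |

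None gives 220. Some combinations come close, but each contradicts the text: alpha 0.025 with no loss allowance (220), the factor 1.1 applied twice (181.5 × 1.21 = 219.6), a loss of about 17% (1 − 182/220 = 17.3%), or an SD of about 1.78.

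**The case against.** The strongest reply is that nothing is lost. The number is larger than the inputs need, the word accepting can be read as setting a ceiling on beta, and 220 with 10% loss keeps beta below 0.2. That stands, and it is why the point is minor. It does not make the sentence right, because the article says "we have calculated that 220 patients will be required in each cohort", and on these inputs 220 are not required.

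A misprint is unlikely, since the Abstract's total of 440 agrees with 220 per cohort. Nor is this an omission that a fuller plan might fill: the inputs and the result are both printed, and they disagree.

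Several stronger readings are tempting, and the document does not support them:

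- *That a stated input must be wrong.* A margin or a decision to round up, left unmentioned, would give 220 with every input intact.
- *That the true SD was about 1.78, or the true loss about 17%.* These values are solved backwards from 220. Other combinations fit about as well, and nothing in the article favours one.
- *That alpha was split between the two principal endpoints.* Alpha 0.025 gives 220 only if the loss allowance is dropped, and the article states both 0.05 and 10%.
- *That the stated 80% power and 10% loss fail to describe the design, or that the cohort is underpowered.* On the stated inputs 220 exceeds the requirement.
- *That the surplus was meant to cover clustering by primary care center.* The article never links the two. Clustering is a separate question, as is whether 1.7 is the SD of the score or of its change; neither bears on whether 220 follows from 1.7.

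**Conclusion.** The point holds in this limited form. The stated inputs require 182 evaluable and about 203 enrolled patients per cohort, whereas the article says 220 (440 in total) were calculated from them. The excess is about 17 per cohort, or 8%. Either an input differs from the one used or an adjustment was left unstated, and the article does not show which. The discrepancy is conservative: taking the inputs as printed, 220 enrolled gives 198 evaluable and about 83% power instead of 80%.

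This rests on the test of two independent means that the article plans, equal cohorts, and independent patients; the 83% would be lower if outcomes are correlated within centers. Severity is minor: the justification is wrong as written, but neither enrolment nor analysis needs to change.

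**What to change.** Keep 220 per cohort and correct the sentence in one of two ways:

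- say that about 203 patients per cohort are required for 80% power, and that 220 will be enrolled, giving about 83% power with 10% loss (without allowance for clustering); or
- state the SD, loss rate or margin that actually led to 220.

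Only the authors know which applies, so the second option should report the calculation that was made, not values chosen afterwards to fit 220. The cost is one sentence, with no change to enrolment.

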### The COPD management model

The COPD PROCESS system was conceived through consensus among all the health-care professionals at different levels of the system; this included agreement on medications between community and primary-care pharmacists. A description of the project has been published [39] and a series of brochures have provided a summary. Clinical practice protocols for each phase of the disease have been defined in accordance with the recommendations of the Global Initiative for Chronic Obstructive Lung Disease (GOLD) [40] and two Spanish national guidelines: the most recent version of the recommendations of the Spanish Society of Pulmonology and Thoracic Surgery (SEPAR) [41] and the consensus paper of the Spanish Society of Family and Community Medicine (semFYC) [42]. The result is a set of algorithms and care pathways reflecting essential diagnostic and therapeutic protocols that have been adapted to conditions in the local health-care system. PROCESS proposes a clinical management program for COPD that places the patient at its center and integrates care within routine clinical practices at different levels. Resources are organized to provide the best possible care and treatment through coordinated multidisciplinary actions (Figure 2).

**Figure 2 F2:**
[figure not shown]
**Participating centers and the care pathways of the COPD PROCESS model**. COPD indicates chronic obstructive pulmonary disease.

Clinical recommendations under the COPD PROCESS model are defined in accordance with patient characteristics and level of disease severity, and the presence or absence of exacerbation. The recommendations, which are not dependent on the setting where health care is delivered, are grouped as follows: 1) prevention (general and specific interventions that target smoking dependency); 2) diagnosis and determination of severity based on GOLD criteria [39]; 3) education (basic information for the patient with COPD); 4) monitoring (periodic follow-up for the patient whose disease is stable and not severe, or stable and severe, or very severe); 5) treatment of exacerbated non-severe and severe COPD; and 6) home care for the COPD patient by means of three programs. The first (the PAD-MPOC-AH program) addresses the needs of the discharged patient. In this program, the primary care team receives discharged patients within the first 72 hours after they arrive home. The second (PAD-MPOC-IF) is designed to manage situations of frequent admission by bringing together primary and specialist health-care professionals in a committee to take charge of the treatment and follow-up of frequently-admitted patients. The third program (PAD-MPOC-VM) will address the needs of patients receiving home noninvasive ventilation.

Each set of recommendations in the PROCESS management model defines interventions and care in the following categories: 1) medical history, physical examination, and diagnostic tests; 2) pharmacologic and non-pharmacologic therapies (smoking cessation, pulmonary rehabilitation, nutritional, education, oxygen therapy, and noninvasive ventilation); and 3) follow-up that is coordinated between the levels of care in accordance with a model of mixed consultation and direct care, including criteria for referral, admission to a conventional hospital ward or treatment in intensive or specialized intermediate care units.

The implementation of the model rests on five types of action that have been undertaken in the preliminary phase. The first involves the formation of working groups and the identification at each primary care center of two referees, a physician and a nurse, who will be responsible for the program at that facility. Second, the physicians and nurses will attend informative sessions at the hospital and primary care center. These sessions will explain the clinical practice protocols and care pathways in the PROCESS management program. This action will also involve explaining the project to the health-care facilities' administrators and managers; official institutional approval and involvement will thereby be assured. The third will involve professional development and training through 1) a session in each primary care center, 2) training for a group of nurses, and 3) the preparation of patient educational support materials. The fourth set of activities will investigate the manner of performing spirometry at each primary care center. Based on the findings, the primary and tertiary care staffs will develop systems for calibrating equipment and assuring the quality of spirometries Training sessions will be set up to show primary care physicians and nurses how to perform and interpret spirometry. The fifth preliminary-phase action will be the introduction of a software application into the medical records of the primary health-care teams. This application will support clinical decision-making in accordance with the PROCESS protocols. This software is currently being developed by the ICS.

These five preparatory actions were begun in 2006. The preliminary phase is scheduled to be completed by the end of 2008, after which the clinical management program will be implemented in its entirety. None of the aforementioned actions will take place in the centers located in the control area of the city's health-care system. Nor will the clinical and organizational interventions be applied there. The care of COPD patients in the control area will continue according to the usual practices of physicians in those centers.

### Study variables

Table 2 shows the variables measured for the study [43-46]. Two complementary dimensions of the PROCESS model will be measured. One involves health-care management. To assess that dimension, clinical and administrative data for the entire population will be extracted from the records of the participating centers. The inclusion of this dimension addresses the issue of the impact on the health-care system (objective 1). The second, clinical dimension will be evaluated on the basis of data from the intervention and control cohorts. For that purpose, data will come from both medical records and visits with patients. The assessment of this dimension corresponds to the evaluation of patient health and quality-of-life benefits (objective 2).

**Table 2 T2:** Study variables for the evaluation of the COPD PROCESS

**Group**	**Variables**
Social and demographic characteristics:^†‡^	Primary care clinic assignment; date of birth; sex.
Patient and lung function characteristics:^‡^	Weight; height; spirometry performed in the past year.
	Spirometry results after bronchodilator (Datospir 120, model A, SIBEL, S.A, Barcelona, Spain; after calibration, with daily maintenance by expert nurses, and quality assurance).
	Carbon monoxide in expired air; pulse oximetry; COPD stage (GOLD criteria); year COPD was diagnosed.
Clinical status (last 6 months):^†‡^	Smoking (frequency, pack-years, cessation phase, enrollment in a cessation program, adherence to recommended preventive measures); exercise (type of activity, duration in minutes and days per week); adherence to any medical advice that has been given; Charlson comorbidity index [43]; dyspnea severity (Medical Research Council Breathlessness scale [44]).
Medication:^‡^	Active principle and pharmaceutical class, dosage.
	Inhalers: number of inhaler devices used in the last month, level of handling expertise (correct performance of 3 actions for a specific inhaler type).
	Oral medications (glucocorticosteroids, theophylline, antioxidants) and their agreement between the patient's report and the medical record.
	Supplemental oxygen therapy; mechanical ventilation; annual vaccination or in the previous winter (flu, pneumococcus)
	Attendance at COPD management training sessions or specific sessions related to medication type.
	Deviations from the PROCESS model (lack of agreement between drugs taken and those recommended for the recorded GOLD severity stage).
Exacerbations in the last year:^†‡^	Defined as the worsening of respiratory symptoms requiring treatment with antibiotics or oral corticosteroids or both (moderate exacerbation) or hospitalization (severe exacerbation) or a combination of the two degrees of severity (based on [45])
Complications and potential complications:^‡^	Primary care nursing diagnosis (according to the Catalan Health Institute's adaptation of the North American Nursing Diagnosis Association (NANDA), February 2003).
Health care in the past year:^†‡^	Primary care clinic visits for any reason (including the general practitioner, the nurse or the respiratory medicine specialist); number of home visits made in the past year; number of visits to hospital (outpatient, emergency, admissions).
Quality of life:^‡^	Respiratory-disease related quality of life (Chronic Respiratory Questionnaire [46])
Systemic inflammatory status:^‡^	C-reactive protein (capillary blood levels: QuikRead^® ^CRP 101. Orion Diagnostica, Espoo, Finland)
Other:^†‡^	Exitus

^† ^Measures evaluating the health-care dimension of the COPD PROCESS model. Information will be gathered on the population of patients with chronic obstructive pulmonary disease in each of the two study areas (clinical and administrative data from the databases of the participating centers).

^‡ ^Measures to evaluate the clinical dimension of the COPD PROCESS model. Information will be gathered on patients in the intervention and control cohorts by consulting patient medical records and arranging for patient visits in each of the centers.

All measurements will be recorded at the start of the study and after 18 months' experience implementing the management program.

### Data collection and analysis

Figure 1 shows details of analysis of the pre- and post-intervention data.

The clinical and administrative information systems at the primary care centers are computerized (eCAP in the ICS centers and other applications such as the OMI-AP or SinAPsis in other centers). Primary care physicians in the intervention area will also be using PROCESS software linked to these applications. That software will serve two functions: it will guide decisions to bring them into line with the PROCESS recommendations and will also provide a place to record the actions taken. The participating hospitals also have computerized clinical and administrative information systems for outpatient, emergency, and day-hospital activity as well as admissions. The data will be merged into a single COPD patient registry for each of the areas (intervention and control). Patients will be identified by their personal identification code. Information in this registry will, if possible, be complemented with information from records of prescriptions for outpatient respiratory therapy, from the Minimum Basic Data Set for discharged patients, from records of pharmaceutical prescriptions filled, and from the death registry of the Department of Health of the Government of Catalonia (Generalitat). Finally, data will also be available from the records of an allied social-welfare and health-services program (Centre Palau).

The clinical data of each patient in each cohort will be collected by two nurses experienced with COPD management who will go to the primary care center of each patient. There they will systematically extract information from the medical records (medical history and other documents in digital form or on paper). They will interview each patient to check the inclusion criteria, obtain informed consent, ask questions relevant to the outcome measures, perform lung function tests, and administer a questionnaire about health-related quality of life.

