### Strengths and possible limitations of the study

The limitations inherent to any evaluative or quasi-experimental study are also present in this research. Patients cannot be randomized for this study. Nonetheless, the design is the most robust one available and will provide the strongest evidence possible, within the existing constraints. Possible differences that might emerge between the control and intervention groups will be adjusted by applying multiple regression analysis.

The use of clinical and administrative databases as sources of information places limitations on the comprehensiveness of the analysis and its validity, as the quality of data is dependent on the information storage interface and its adequate and proper use by health-care professionals. It was expressly decided, however, not to create dedicated databases given that the pragmatic nature of the model requires that the information sources be integrated into the daily work routines of the physicians and nurses who are caring for the patients. The inclusion of the study cohorts will counterbalance this limitation.

Implementing a multidisciplinary model over such an extensive geographic area and working with such a large number of clinical caregivers is a complex undertaking. Adequate and consistent adherence to the PROCESS protocols at all the health-care facilities will require a very high level of dedication. Therefore, it will be essential to integrate the project-specific software into the records of the care facilities. Periodic meetings to coordinate and supervise the participants will also be required.

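### Record-derived secondary outcomes come from databases that gain a PROCESS recording tool in the intervention area only, so a change in recording can pass for, or hide, a programme effect

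*Protocol article*

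**What the plan says.** **Source of the outcomes.** Under *Study variables*, for the health-care dimension, "clinical and administrative data for the entire population will be extracted from the records of the participating centers". Table 2 marks clinical status (smoking, exercise, adherence to advice, comorbidity, dyspnea) and exacerbations as measures for both the area populations and the cohorts. An exacerbation is "Defined as the worsening of respiratory symptoms requiring treatment with antibiotics or oral corticosteroids or both (moderate exacerbation) or hospitalization (severe exacerbation"); mixtures of these grades count as well.

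**The recording tool.** *The COPD management model* lists as its fifth preparatory action "the introduction of a software application into the medical records of the primary health-care teams". *Data collection and analysis* adds: "Primary care physicians in the intervention area will also be using PROCESS software linked to these applications". The software guides decisions and "will also provide a place to record the actions taken".

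**The control area.** "None of the aforementioned actions will take place in the centers located in the control area of the city's health-care system".

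**The contrast.** *Statistical analysis* compares the groups on change from before to after the intervention, for process and outcome variables alike.

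**The acknowledged limitation.** *Strengths and possible limitations of the study* accepts that database quality depends on the storage interface and how professionals use it. It then states: "The inclusion of the study cohorts will counterbalance this limitation". For the cohorts, "data will come from both medical records and visits with patients".

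**The concern.** The programme changes the instrument that measures some of its own outcomes, and it does so in one area only. A pre-post comparison between areas removes recording differences that are stable over time. It does not remove a recording change that starts with the programme in one area.

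Moderate exacerbations are the clearest case. They are defined by treatment, and treatment given is an action of the kind that the software offers a place to record. If such events are entered more completely after the start, the counted rate rises in the intervention area without any true increase, and a real benefit can be hidden. For recorded process items, fuller entry could work the other way and flatter the programme. A reader could not correct for this with a single sign.

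The limitations section names the general mechanism, dependence on the interface, but does not say that the interface changes in one area only. That one-sidedness turns a data-quality problem into a possible bias in the comparison.

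**Working it through.** The plan gives no figure on recording completeness, so there is nothing to reproduce. The check has two parts.

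**1. Does the design separate recording from effect?**

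- Before, control area: usual systems.
- After, control area: usual systems.
- Before, intervention area: usual systems, possibly with the tool already in place for part of the baseline year, since it is introduced in the preparatory phase.
- After, intervention area: usual systems plus the PROCESS tool.

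Let s be the share of true events that is recorded. Then

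observed ratio of rate ratios = true ratio × (s_post / s_pre, intervention) ÷ (s_post / s_pre, control).

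On the log scale the recording term sits in the area-by-period interaction, which is also the programme effect. Adjusting for patient characteristics leaves it there, because recording follows area and period and not the patient.

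**2. How large could it be?**

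All recording shares are assumed, and the control area is held constant.

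| Recorded before → after, intervention | Apparent ratio, no true effect | Apparent ratio if the true ratio is 0.80 |
|---|---|---|
| 80% → 90% | 0.90/0.80 = 1.13 | 0.90 |
| 70% → 80% | 0.80/0.70 = 1.14 | 0.91 |
| 60% → 75% | 0.75/0.60 = 1.25 | 0.80 × 1.25 = 1.00 |
| 70% → 90% | 0.90/0.70 = 1.29 | 1.03 |
| 60% → 80% | 0.80/0.60 = 1.33 | 1.07 |
| 50% → 90% | 0.90/0.50 = 1.80 | 1.44 |

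A fall in recording reverses the sign: 80% → 70% gives 0.70/0.80 = 0.88.

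*Overlap with baseline.* If the tool were already in use for half the baseline year, the 70% → 80% case would have a baseline average of (0.70 + 0.80)/2 = 0.75. The ratio would be 0.80/0.75 = 1.07. The bias is diluted but not removed.

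*Precision.* Take the article's expected patient numbers (32,114 and 32,248), an assumed one exacerbation per patient-year and simple Poisson error. For 70% → 80%:

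- SE of the log ratio = √[1/(32,114 × 0.70) + 1/(32,114 × 0.80) + 2/(32,248 × 0.70)] = 0.0131
- z = ln(0.80/0.70)/0.0131 = 0.1335/0.0131 ≈ 10.2

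For 70% → 72% the same formula gives z ≈ 2.1. At 0.5 and 1.5 events per patient-year, z is 7.2 and 12.5 for 70% → 80%, and 1.5 and 2.6 for 70% → 72%.

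Fewer patients will carry a recorded diagnosis. The *Background* cites 78.2% of cases as previously undiagnosed. With the remaining 21.8% (0.218 × 32,114 ≈ 7,000 per area), z scales by √0.218 = 0.467, to about 4.7 for 70% → 80% and 1.0 for 70% → 72%. Overdispersed counts would lower all these values. A moderate shift could still look like a precise effect; a very small one need not.

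**The case against.** The strongest reply is that nothing central is touched. Admissions can be taken from the hospitals' own computerized systems, which run in both areas, and study nurses administer the CRQ. The objective 1 analysis names utilization, visits and admissions; it names no area-wide analysis of exacerbations, exercise or dyspnea. The authors disclose that their data depend on the interface, rejected dedicated databases deliberately, and provide cohorts whose members are interviewed. Rules for deriving events from merged sources may stand in a full protocol or analysis plan that is not shown.

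Most of this stands as a limit on scope. A reader might infer that the main endpoints are biased; the documents do not support that. The cohort interview is a real partial safeguard.

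Other tempting readings also go too far:

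- That neither area has the tool at baseline. The article does not say so, and introduction in the preparatory phase could overlap the baseline year.
- That an exacerbation counts only if its treatment is recorded. Table 2 speaks of events requiring treatment or hospitalization and gives no counting rule.
- That exercise and adherence must appear to improve. Fuller recording can fill gaps in either direction, and no specific fields for these items are described.

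What does not fall away is the structure. Table 2 assigns these variables to the area databases, the general statement on group comparisons covers process and outcome variables, and the tool is one-sided. Cohort data still come partly from the same records, and the article does not say which source prevails. This is more than missing detail, because the article itself fixes the source, the one-sided tool and the claimed counterbalance.

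**Conclusion.** The point holds for record-derived secondary outcomes: moderate exacerbations and the area-wide clinical status items in Table 2. For these, a change in recording completeness can appear as a programme effect or hide one, and the planned regression cannot tell the two apart. It does not directly reach respiratory admissions, the CRQ, deaths or severe exacerbations.

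Whether recording will change, in which direction and by how much cannot be known from the document. The ratios of 1.14 (70% to 80%) and 1.25 (60% to 75%) illustrate sensitivity; they are not estimates. They assume constant recording in the control area and no tool use in the baseline year. The cohorts reduce the problem but do not fully counterbalance it. The plan should be changed, because following it as written could give a wrong secondary result.

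**What to change.** 1. Exclude fields filled only through the PROCESS software from between-area outcome comparisons. Use them to describe implementation.
2. Base the between-group comparison of smoking, exercise, adherence and dyspnea on the cohort interview at both visits. Treat the database versions as descriptive.
3. For area-wide exacerbations, use hospital discharges plus, where access is obtained, filled prescriptions for antibiotics or oral corticosteroids, in both areas and both periods. Label the latter as treated-course counts, because indication and symptoms are missing and PROCESS may itself alter prescribing. If access is not obtained, report recording completeness by area and period and label the comparison as exposed to recording change.

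The first two items cost wording only, since the interview is already planned. The third depends on sources that the article adds to the registry only if this proves possible, so access has to be secured. The price is a less specific exacerbation measure and less area-wide detail on secondary outcomes.
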